### Patients

Forty patients accepted for ECT at Haukeland University Hospital will be included. After inclusion of 8 patients, the protocol was slightly revised and the remaining 32 patients will follow the protocol as described here.

### Inclusion criteria

Patients (age > 18) referred to the ECT-unit and accepted for treatment because of moderate and severe depression, fulfilling the criteria for the following ICD-10 diagnoses: F31.3 and F31.4; F32.1 and F32.2 and F32.3; F33.1 and F33.2 and F33.3. In addition the symptom intensity must be verified by a score ≥ 25 on the Montgomery and Åsberg Depression Rating Scale (MADRS). There is no upper age for participation; however, the responsible clinician will consider if patients are eligible for inclusion (functioning, enable to give written informed consent).

### Exclusion criteria

ECT treatment within the last 12 months. Pregnancy. Patients unable to give written informed consent (according to the responsible clinician or ECT responsible). Patients who cannot participate in the MRI scanning because of contraindications to MRI.

### Control groups

There will be two control groups; a group of patients undergoing ECV for AF (*controls 1*) and healthy controls undergoing the same investigations as the ECT patient group, but not receiving ECT or anesthesia (*controls 2*).

### Controls 1

In order to control for the potential effect of anesthesia on MRI images (particularly with regard to the spectroscopy) and blood samples, 15 patients referred for ECV of AF will be recruited. This is a patient group that receives similar anesthesia to ECT patients. This control group will have 2 MRI scans; one 1-2 hours before ECV and another MRI 1-2 hours after ECV. Blood samples will also be collected for the biobank at time points indicated in Figure 1. In addition to being a control group, data that is acquired will be used in a pilot investigation of potential effects of ECV of AF, if there are silent emboli to the brain. Such emboli would readily be detected on the diffusion images. Antithrombotic treatment must be Warfarin with an INR value above 2,0 at all measurements for the last 3 weeks prior to DC cardioversion or absolute compliant everyday use of Non-vitamin K antagonist oral anticoagulants (NOACs) for 3 weeks. There will be no changes in the treatment of their AF, patients are only asked to participate in additional examinations (MRI, blood samples) before and after ECV.

### Controls 2

When analyzing longitudinal MRI data, it is important to control for effects on imaging parameters that are a consequence of repeated measurements/time, rather than effects of the treatment. 15 healthy, age and gender-matched volunteers will be recruited for repeated MR imaging, blood samples and neuropsychological testing; following the protocol for the ECT patients (see Figure 1) but with no ECT or anesthesia.

### ECT treatment

ECT will be administered with a Thymatron System IV Somatics Inc. providing brief-pulse, square wave, constant current.

#### Anesthesia

Anesthesia will be obtained with either the short acting anesthetic thiopental or propofol. All patients will be hyperoxygenated with oxygen-enriched air 1 to 2 minutes before and during the initiation of anesthesia to optimize induction of seizures [62,63]. Other medication necessary during anesthesia (e.g. for premedication or termination of prolonged seizure) will be left to decision by the anesthesiologist.

#### Stimulation electrodes placement

Stimulation electrodes will be placed ad modem d’ Elia [64] (Right unilateral electrode placement, RUL), as high dosage ECT with unilateral placement of stimulation electrodes has shown to be as effective as bilateral placement [65,66]. Three sessions per week will be given until remission, with a maximum of 18 sessions.

#### Stimulus

The duration of the stimulus pulse will be set to 0.5 ms. The initial stimulus energy will be determined by an age based method, where the energy (E) is calculated as following [67]: Patient’s age in years × 5 ≅ stimulus charge in mC. The Thymatron delivers a charge of 25.2 to 504 mC in 20 equal steps, set by the % Energy dial. According to the above formula this makes: Patient’s age in years ≅ % Energy. In order to consider gender specific differences in seizure threshold, the % Energy was adapted as following: For male patients: % Energy + 5 to 10%. For female patients: % Energy - 5 to 10%.

#### Seizure adequacy

The adequacy of each seizure will be evaluated by the ECT-clinician based on seizure duration, δ-waves, reorientation time and clinical effect. The treatment should be followed by a comatose state, from which consciousness is gradually regained [68]. If a sufficient seizure was not obtained in one session the patient will be either re-stimulated in the same session or/and stimulus parameter will be adjusted in the next session.

### Clinical assessments and Neuropsychological tests

Clinical assessments and monitoring will be performed largely in accordance with a recently used protocol [69], as detailed below and summarized in Table 1.

Patients will be diagnosed on the basis of a clinical interview supported by information from hospital records. The diagnoses will be subsequently verified by the Mini-International Neuropsychiatric Interview (MINI; specifically the MINI-Plus) [70]. Symptom intensity will be measured with MADRS [71] and the Clinical Global Impression (CGI) [72].

Patients will be assessed before the treatment, and weekly during the ECT-series with the Mini-Mental State (MMS) by their treating clinician.

A neuropsychological test battery that includes both standardized and normalized tests and experimental methods to assess memory, attention, psychomotor speed and executive functions, will be applied at inclusion, after treatment and at follow up, as listed in Table 1. The neuropsychological assessment will consist of standardized tests measuring cognitive functioning within verbal and visual memory with California Verbal Learning Test-II (CVLT-II) Rey Complex Figure Test (RCFT) and Digit span from Wechsler Adult Intelligence Scale, Revised (WAIS-R), executive functioning with Wisconsin Card Sorting Test (WCST), and test from the Delis –Kaplan Executive Function System (D-kefs): Color-Word Interference Test (CWIFT), Verbal fluency (VF), Tower, Trailmaking test (TMT), attention measured with Conners’ Continuous Performance Test-II (CPT), Digit symbol from WAIS-R and motor speed (Pegboard), in addition to general levels of intellectual ability Wechsler’s Abbreviated Scales of Intelligence (WASI). Autobiographical memory will be assessed by using the Autobiographical Memory Interview-Short Form (AMI-SF).

### Dichotic listening task

Placement of electrodes on the non-dominant side (unilateral stimulation) is important to reduce cognitive impairment as a side effect of ECT treatment [65,73]. Traditionally, hemispheric dominance is evaluated by handedness measures, which however is a crude measurement when it comes to subtle differences in function between the cerebral hemispheres. It is therefore suggested to use a neuropsychological task, dichotic listening, which has been shown to be comparable in sensitivity to reveal functional differences between the hemispheres to the Wada test [74,75]. We will apply the Bergen dichotic listening test [76] both as a measure of language dominance and as an effect parameter, i.e. as a measure of cognitive control since it has been shown that varying instructions about attention focus while performing the dichotic listening task reveals capacity for cognitive control [77]. A recent development makes it possible to deliver the test bedside, by use of an application on a hand held device; iDichotic, Bergen fMRI group [78]. The prediction is that treatment response correlates with improved results for the instruction condition that requires highest cognitive control.

### MRI acquisition and post processing

Imaging will be performed at 4 time points: ~1-2 hours before and ~1-2 hours after ECT, ~ 7-14 days after ended treatment and at follow-up 6 months after ended treatment. The same MRI protocol will be applied at each time point (Figure 1).

#### MRI Protocol

Initial imaging will be performed on a 3T GE Signa HDxt system with 8 channel head coil, but most of the subjects will be scanned on a 3T Discovery MR750 system with 32 channel head coil. The protocol (details specified for the MR750 system) includes a T1-weighted fast spoiled gradient echo, FSPGR (TE/TR = 2.9/6.7 ms; TI = 600 ms, flip angel = 8°; FOV = 25.6 cm; voxel size = 1.0 × 1.0 × 1.0 mm^3^, acquisition time = 10:32 min.); a T2-weighted CUBE FLAIR sequence (TE/TR = 129/6000 ms; TI = 1855 ms; FOV = 25.6 cm; voxel size = 1.0 × 1.0 × 1.0 mm^3^, acquisition time = 08:51 min.); for RSI, a single-shot pulsed-field gradient spin-echo EPI sequence (TE/TR = 85/7000 ms; FOV = 24 cm, matrix = 96 × 96 × 55 with 4 b-values (*b* = 0, 500, 1000 and 4000 s/mm^2^ and 6, 6 and 15 unique directions for the nonzero b-values, respectively), acquisition time = 3:30 min.); for SWI a gradient recalled echo 3D Ax SWAN sequence (TE/TR, 23/37 ms; slice thickness 2 mm; acquisition time 3:30 min.). For ^1^H-MRS, both single-voxel point-resolved spectroscopy, SV PRESS, and a spectral editing method, MEGA-PRESS [79], will be used. The SV-PRESS (TR = 1500 ms, TE = 35, 128 scans; acquisition time = 3:48 min.) voxel will measure 2 × 2 × 2 cm^3^ and the placement alternate between right and left anterior cingulate cortex (ACC) for each new patient. For MEGA-PRESS (TR = 1500 ms, TE = 68 ms, 192 scans, acquisition time = 10:06 min.) the voxel will measure 3 × 3 × 3 cm^3^ and cross the mid-line, covering both right and left ACC in every patient.

#### Image processing and analysis

Structural data will be analyzed using FreeSurfer [42] and Quarc [80]. In a preprocessing step, structural images will be corrected for distortions caused by gradient non-linearity [81], diffusion weighted (DW) images will be corrected for motion, eddy currents and magnetic susceptibility artifacts [82,83] and the DW volume will be co-registered to the structural volumes. SWI data will be analyzed using Statistical Parametrical Mapping (SPM8/SPM12) analysis software package (Wellcome Department of Cognitive Neurology) running under MATLAB (Mathworks). RSI data will be analyzed using custom made software and processing and/or with FSL [84,85] and MRS data by using LCModel Software [86]. SPSS will be used for statistical analyses.

Analysis methods and software may change if newer versions or other software is found to be more suitable than the above mentioned.

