Increased levels of BDNF has been reported following ECT [34], and BDNF has been suggested as a potential biomarker for depression [35]. Neurogenesis has been shown to occur in the dentate gyrus of the hippocampus in adult humans [36], and ECT-induced neuroplasticity is gaining more focus as a framework for understanding the effects of ECT [23]. A few studies of humans have reported increased hippocampal volumes and/or other structural changes following ECT [37-41]. Nordanskog et al. [39,41] performed manual segmentation without complete blinding of the MRI time point that was traced (before or after ECT), introducing a potential observer bias. Dukart et al. [38] used voxel-based morphometry, while Tendolkar et al. [40] and Abbot et al. [37] both used FreeSurfer [42] for volumetric segmentation and analysis. Compared with these studies we will recruit more patients, use state of the art automatic segmentation procedures, and radiology readers will be blinded to study group and the time point of MRI scans. In addition, by applying multimodal imaging, structural changes can be assessed with respect to changes in diffusion properties, susceptibility weighted imaging (SWI) and fluid attenuated inversion recovery (FLAIR) imaging. Our design will allow longitudinal tracking of brain changes; 1-2 hours after the first ECT, after treatment completion and at 6 months follow up.

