### ECT and harmful effects

ECT has been a controversial treatment from its introduction. The most important side effects are related to memory impairments [6] and it is recommended that the patients’ cognitive functioning is monitored both during and after treatment [16]. A recent randomized controlled trial in treatment-resistant bipolar depression found reduced autobiographic memory consistency after ECT but no deterioration of general neurocognitive function [13]. Structural damage to the human brain has to our knowledge, never been documented to be caused by ECT. Case studies with rare complications, such as subdural hematoma, have been published [56], however a study using cerebral Computer Tomography in 40 patients before and after ECT detected no changes caused by ECT, even with convulsions lasting several minutes [57]. Both conventional MRI and diffusion weighted imaging (DWI; a sequence that is sensitive to edema) have failed to find structural damage [58]. However, changes on DWI have been shown for patients after status epilepticus [59]. If brain injury occurs as a consequence of ECT, one may expect to find micro hemorrhages. SWI is extremely sensitive to hemorrhages, and is routinely used in imaging of stroke [60]. However, SWI, as an indicator of microvascular dis-integrity, has to our knowledge never been applied after ECT. In addition, by using ^1^H-MRS we will measure N-acetylaspartate (NAA), which is primarily localized in neurons and considered a marker for neuronal integrity [61].

Our project will use high field strength, state of the art MRI and combine RSI, SWI and ^1^H-MRS which should enable detection of more subtle post-ECT effects.

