### Hypotheses and aims

Based on the above discussions, the following main hypotheses define the outline and aims of this project:Hippocampal volumes increase after ECT treatment. A) Specifically there is increased volume of the dentate gyrus, which would suggest that the increase is caused by neurogenesis. B) Changes in hippocampal structure correlate with treatment response, neurocognitive measures and increased concentrations of neurotrophic factors in blood samples.ECT causes increased levels of the neurotransmitter GABA and changes the glutamate/GABA balance. A) GABA concentrations correlate with treatment response. B) Genes regulating GABA synthesis and cycling are up-regulated or activated. C) A subset of cortical projections is strengthened; a possible mechanism causing reduced connectivity in frontal areas.ECT does not cause measurable signs of harmful effects to the brain. A) No changes are detected on microvascular (SWI) and microstructural (RSI) imaging. NAA (measurend in the ACC) is unaffected. B) Possible immediate post-ECT effects, e.g. edema, that is detectable by diffusion weighted imaging, are reversible.

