### For patients and controls

Participation in the project will for the patients include MRI scans (4 time points) and blood samples (5 time points) as well as neuropsychological testing (3 time points) that are not part of the standard treatment regimen. For *controls1* (AF-ECV) participation will include MRI (2 time points) and blood samples (2 time points) that is not part of the standard clinical treatment. For *controls2* participation will require MRI scans (4 time points) and blood samples (5 time points) as well as neuropsychological testing (3 time points). *Controls2* will be economically compensated for participating.

There are no known adverse effects related to MRI scanning when standard safety procedures are followed. However, scanners are noisy and scans will last up to one hour. Blood samples will require venous puncture. A neuroradiologist will screen the first MRI scan for each participant. In the case of incidental findings of relevant pathology, the participant will be offered referral to medical consultation.

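### The only analysis named for SWI is SPM, which as a group voxel-wise map has almost no power for scattered micro-hemorrhages; a blinded per-patient count of new lesions should be the SWI harm outcome

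*Protocol article*

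**What the plan says.** All references are to the protocol article.

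- **Target.** *ECT and harmful effects* states: "If brain injury occurs as a consequence of ECT, one may expect to find micro hemorrhages". It justifies the sequence in these words: "SWI is extremely sensitive to hemorrhages, and is routinely used in imaging of stroke".
- **Hypothesis.** In *Hypotheses and aims*, the third main hypothesis is "ECT does not cause measurable signs of harmful effects to the brain", and part A begins "No changes are detected on microvascular (SWI) and microstructural (RSI) imaging". No margin is attached. The *Discussion* puts microvascular integrity first among its questions.
- **Analysis.** *Image processing and analysis* assigns software to most of the imaging data. For SWI it says: "SWI data will be analyzed using Statistical Parametrical Mapping (SPM8/SPM12) analysis software package". It gives no group model, threshold, lesion count or rating rule for SWI. It names SPSS for statistics and adds: "Analysis methods and software may change if newer versions or other software is found to be more suitable than the above mentioned".
- **Human reading.** *Hippocampal volume* says that "radiology readers will be blinded to study group and the time point of MRI scans". *For patients and controls* says: "A neuroradiologist will screen the first MRI scan for each participant". The latter is a check for incidental findings.
- **Power.** *Power analysis* reports that no study was found from which SWI power could be estimated.

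**The concern.** The harm being sought is a focal event in an individual patient. In its ordinary statistical use, SPM tests whether the average change at a given voxel differs from zero, or between groups. New microbleeds at different places in different brains contribute to different voxels. At each voxel one large value among many near-zero values raises the mean and the standard deviation together, so the test statistic stays small.

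The direction of the failure matters. Hypothesis 3A is supported by non-detection, so a method that rarely detects scattered lesions would appear to support it even if new microbleeds were common.

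**Working it through.** **1. The plan's own figures.** No sample size or power is stated for SWI, so there is no SWI figure to reproduce. The two sample sizes that are stated do reproduce (paired t-test, two-sided 5%, power 0.80). GABA, 0.6/0.5 = 1.20, needs 8 (power 0.828). Right hippocampus, 133/123 = 1.081, needs 9 (power 0.810). They do not bear on SWI.

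**2. Ceiling of a group map.** Input: n = 40 ECT patients (*Patients*; *Power analysis*). Suppose k patients have a new lesion of signal δ at the same voxel and the other n − k show exactly no change.

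- mean = kδ/n
- s² = δ²k(n − k)/(n(n − 1))
- t = mean/(s/√n) = √(k(n − 1)/(n − k))

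δ cancels, so a stronger lesion does not help.

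| k of 40 at the same voxel | t |
|---|---|
| 1 | √(39/39) = 1.00 |
| 4 | √(156/36) = 2.08 |
| 8 | √(312/32) = 3.12 |
| 9 | √(351/31) = 3.36 |
| 11 | √(429/29) = 3.85 |
| 14 | √(546/26) = 4.58 |
| 16 | √(624/24) = 5.10 |

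One-sided uncorrected p < 0.001 with 39 degrees of freedom needs t = 3.31, so k = 9. Bonferroni thresholds (two-sided 5%) are 3.80 for 100 independent locations and 4.56 for 1000, so k = 11 and k = 14. An assumed family-wise threshold of t = 5 needs k = 16. If all 40 patients bled at different sites, the noise-free t would be 1 at each of those sites.

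**3. With noise.** A corrected map of paired change in 40 patients was simulated with lesions placed at random. The article gives none of the settings, so these ranges are assumptions:

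- 100, 500 or 1000 independent locations
- 10, 25, 50 or 100% of patients affected
- 1, 3 or 5 new lesions per affected patient
- lesion signal of 3, 5 or 10 noise SDs
- 400 runs per setting

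The rejection rate lay between 0.01 and 0.10 throughout, around the nominal 0.05. Overlap explains this: 40 patients with 5 lesions each give on average 40 × 5/100 = 2 lesions per location with 100 locations and 0.2 with 1000, against the 11 to 14 needed.

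**4. A per-patient count instead.** Detection is assumed to be perfect.

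- Chance of at least one affected patient among 40 at a true rate of 10%: 1 − 0.9⁴⁰ = 0.985. At 5% it is 0.87 and at 2% it is 0.55.
- Two-sided 95% upper limit with 0/40 affected: 1 − 0.025^(1/40) = 8.8%. With 0/32 (the patients who follow the protocol as described) it is 1 − 0.025^(1/32) = 10.9%.
- Fisher exact test, 40 ECT patients against 15 healthy controls with an assumed control rate of zero: power 0.005, 0.27, 0.80 and 0.98 at true rates of 10, 20, 30 and 40%.

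**The case against.** The strongest reply is that the article names a software package and not a test. SPM can also serve for registration or within-patient comparison, and the words group map or voxel-wise do not appear. This stands, so the conclusion above is conditional on the usual use. It does not remove the point, because SPM is the only method attached to SWI and no lesion-level SWI outcome is stated.

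A reader might infer that follow-up scans will not be read for lesions at all, because the neuroradiologist's screen covers only the first scan. The article does not support this. That screen is a safeguard for incidental findings. Masking readers to time point makes sense only if they see scans from several time points. Nor is the software list complete: it has no line for FLAIR, or for the silent emboli to be sought in the cardioversion controls. Visual detection is therefore not excluded. It is simply not tied to an SWI outcome.

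A reader might also infer that the whole harm analysis will return no change whatever happens. That goes too far. RSI, NAA and diffusion imaging are separate parts of Hypothesis 3, and a group map could still show a diffuse or spatially consistent SWI change.

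Finally, lesion definitions and reading rules may sit in a full protocol or analysis plan that is not shown, and their absence here is no fault. The point is the method the article does name, which does not fit the lesion it names. The clause that lets methods change does not settle this, since a harm method chosen later, possibly with data in view, weakens a claim of no harm.

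**Conclusion.** The point holds in conditional form. If SPM is used as a group voxel-wise comparison, its power for focal lesions at varying sites is close to its false-positive rate (0.01 to 0.10 in the simulated settings). Without noise, about 9 of 40 patients would need a lesion at the same voxel for one-sided uncorrected p < 0.001, and 11 to 14 for the corrected thresholds examined. A null SWI map would then say almost nothing about micro-hemorrhage and should not be read as support for the SWI part of Hypothesis 3A.

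The figures assume 40 complete pairs of scans, lesions without a preferred site, and independent locations. Spatial smoothing was not modelled separately; the coarse setting of 100 locations suggests that it would not rescue the map. The conclusion does not extend to RSI, NAA or diffusion imaging.

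**What to change.** - Name as the SWI harm outcome, per participant, the presence (yes/no) and number of new microbleeds from visit 2 to visits 3, 4 and 5.
- Have the radiology readers already foreseen score it on all time points in random order, without knowledge of group or visit.
- Report the proportion of ECT patients affected with an exact confidence interval as the main result, so that a finding of none is stated with its upper limit.
- Treat the comparison with the 15 healthy controls as supportive only, given its low power.
- Keep SPM as a secondary analysis of diffuse or spatially consistent susceptibility change, and state the model used.

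The scans are already scheduled and the readers already planned. The cost is a change of analysis wording and added reading time on the follow-up SWI series.
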